### Measures of outcome

The primary outcome measure is the rate of systemic antibiotic use per 1000 days of hospitalization (see details under Sample size calculation and statistical considerations). Secondary outcome measures are as follows (for all episodes of hospital acquired infection with positive blood cultures for the first 7 days following initiation of antibiotics after adjusting for important possible patient confounders): number of days free from mechanical ventilation (an indicator of respiratory failure); number of days free from inotropic support (an indicator of circulatory failure); costs for specific expensive medications (e.g. fresh frozen plasma); and nurse allocation (an indicator of treatment intensity).

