To assess the clinical efficacy of the new diagnostic measures, we suggest that a randomized controlled trial be conducted comparing two management strategies. The control strategy will consist of routine management, with the exception that physicians are requested to provide a probability estimate for the presence of bacterial infection whenever a diagnostic work up (blood cultures or tracheal aspirate culture) is ordered. The intervention strategy will consist of cytokine measurement from the sample and provision of a result based post-test probability within a few hours after sample collection. The null hypothesis states that the management arms will not differ with respect to antibiotic utilization rate, measured as the number of days on systemic antibiotic treatment per 1000 days of hospitalization. The secondary null hypothesis states that the arms will not differ with respect to costs associated with hospital acquired septic shock.

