### Eligibility criteria for participants

All patients admitted to the interdisciplinary neonatal or paediatric intensive care unit (ICU) of the Children's Hospital of Zurich are eligible. Patients who are referred to other wards within 24 hours after admission will be excluded from data analysis, because in these patients the decision to stop antibiotic treatment is no longer the responsibility of participating intensivists.

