#### Intervention strategy

If patients are randomized to the intervention arm, then physicians are also obliged to document their best estimate of the probability that the patient has sepsis or pneumonia, again on two logarithmic visual-analogue scales (range 0–100%). This documentation is again mandatory and must be marked on the laboratory form (Fig. 1). In the intervention arm, blood or tracheal aspirate specimens are analyzed and results are returned to the unit before 1 p.m. Physicians receive the raw cytokine values as well as the calculated likelihood ratio and the post-test probability (Fig. 2). This information is provided in addition to routinely available data. Provided that the available post-test probability indicates absence of infection, physicians are encouraged to stop antibiotic treatment. It is suggested that antimicrobial therapy be continued if the post-test probability indicates infection. It is important to note that the protocol provides only 'suggestions', and that the final decision regarding therapy is left to the discretion of the responsible clinician. This is similar to clinical routine, in which diagnostic results may suggest alterations to treatment decisions but they do not dictate treatment.

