### Objectives and hypotheses

Our objectives are to achieve a clinically relevant reduction in overall antibiotic use and to reduce treatment costs caused by delayed diagnosis of nosocomial infection. In this study we will test the hypothesis that routine surveillance by determination of cytokine levels in plasma and tracheal aspirates will allow safe discontinuation of antibiotic therapy within 24 hours if the proposed laboratory prediction model indicates absence of infection. We regard a reduction in antibiotic exposure by 15% to be a clinically relevant effect. The second hypothesis we will test is whether early diagnosis reduces the morbidity and costs associated with hospital acquired infection. Ascertaining relevant indicators of morbidity and costs in all patients with culture proven bloodstream infection will operationalize this.

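### The safe-discontinuation hypothesis covers any worked-up patient, but no declared outcome measures harm in bloodstream infection present on admission

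*Protocol article*

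**What the plan says.** Under Objectives and hypotheses, the first hypothesis is that cytokine surveillance "will allow safe discontinuation of antibiotic therapy within 24 hours if the proposed laboratory prediction model indicates absence of infection". The second is separate: "The second hypothesis we will test is whether early diagnosis reduces the morbidity and costs associated with hospital acquired infection". The sentence after it reads "Ascertaining relevant indicators of morbidity and costs in all patients with culture proven bloodstream infection will operationalize this".

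Measures of outcome lists ventilator-free days, inotrope-free days, costs of expensive drugs and nurse allocation. All four are taken "for all episodes of hospital acquired infection with positive blood cultures for the first 7 days following initiation of antibiotics". The Introduction words the secondary null hypothesis differently again: "the arms will not differ with respect to costs associated with hospital acquired septic shock".

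On who is exposed, Eligibility criteria states: "All patients admitted to the interdisciplinary neonatal or paediatric intensive care unit (ICU) of the Children's Hospital of Zurich are eligible". Only patients moved to another ward within 24 hours leave the analysis. Intervention strategy adds: "Provided that the available post-test probability indicates absence of infection, physicians are encouraged to stop antibiotic treatment", with the proviso that "the final decision regarding therapy is left to the discretion of the responsible clinician".

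Data collection says that mortality will be recorded but will not be a study outcome. It also has a study nurse record clinical data around culture collection in both groups.

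**The concern.** The gain from the strategy, fewer antibiotic days, is counted in all analysed patients. Morbidity is counted only in hospital acquired, blood-culture-positive episodes. A newborn or child admitted with suspected sepsis can be worked up on the first day and receive a low post-test probability. If that patient is in fact bacteraemic and treatment is stopped, the saved antibiotic days favour the intervention and any resulting deterioration enters no declared outcome.

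At stake is the word *safe* in the first hypothesis. The trial could report a reduction in antibiotic use and call discontinuation safe without a planned comparison of harm in infections that were present on admission.

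**Working it through.** The point rests on comparing sections; no calculation decides it. The plan's one sample size was checked first, to see whether it bears on the matter.

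**The plan's figure.** Inputs from Sample size calculation: 40% on antibiotics, a 10% reduction (read as relative, so 36%), type I error 5% (taken as two-sided), power 80%. With mean proportion 0.38:

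n = [1.960·√(2·0.38·0.62) + 0.842·√(0.40·0.60 + 0.36·0.64)]² / 0.04² ≈ 2311 days per arm.

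The plan states 2300, so the figure reproduces; power at 2300 is 79.8%. It rests on the primary outcome alone. The population chosen for morbidity does not alter it.

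**Scope of each element, by origin of infection.**

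1. *Discontinuation hypothesis* (Objectives and hypotheses): no limit.
2. *Eligibility*: all ICU admissions, so infections present on admission are included.
3. *Encouragement to stop* (Intervention strategy): depends on the post-test probability only; no limit.
4. *Primary outcome* (Measures of outcome): antibiotic use per 1000 hospital days; no limit.
5. *Secondary outcomes* (Measures of outcome): hospital acquired, blood-culture-positive episodes only.
6. *Mortality* (Data collection): recorded, not an outcome.
7. *Three further analyses* (Sample size and statistical considerations): prescription prevalence and antibiotic-free days. These measure antibiotic use, not harm.

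Items 1 to 4 include bacteraemia present on admission. Item 5 leaves it out, and items 6 and 7 supply no declared harm outcome in its place.

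**Can a falsely low result arise in such a patient?** The Pilot study section gives ROC values of 0.88 and 0.85, so discrimination is good but imperfect. The Introduction claims near-exclusion at low plasma levels for Gram-negative sepsis only. Results are returned before 1 p.m., whereas the control strategy waits 48 hours on negative cultures. A suggestion to stop can therefore reach the physician before a culture turns positive.

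**Size.** The article gives no count of bloodstream infections, in total or by origin. The share outside the secondary outcomes cannot be derived.

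**The case against.** The strongest reply is that the secondary outcomes were never meant to monitor harm. They test whether earlier diagnosis reduces nosocomial morbidity and cost, and restricting them to hospital acquired episodes suits that question. This stands, and it is why that population should be kept. It does not supply an outcome for the first hypothesis, which claims safety.

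A reader might infer that Objectives and hypotheses contradicts Measures of outcome. The text does not support so strong a reading. The operational sentence points back to the one before it, which concerns hospital acquired infection, and the Abstract, Introduction and Discussion also speak of nosocomial or hospital acquired infection. The wording is loose. Nor does it cause the gap, which would remain if the sections matched word for word.

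A reader might also infer that every work-up can lead to a suggestion to stop. It cannot. Samples must arrive by 10 a.m. on one of 15 pre-specified working days a month, the result must indicate absence of infection, and the clinician may overrule it. Only infected patients with a falsely low result are at issue.

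Finally, harm is not unobserved. Mortality and clinical data around cultures are recorded in both groups, and restarted antibiotics would show in the antibiotic-free-day analyses. The gap lies in the declared outcomes, not in the data.

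**Conclusion.** The point holds in limited form. The article hypothesizes safe discontinuation without regard to origin of infection, yet declares no outcome for harm in bacteraemia present on admission, although those patients' antibiotic days enter the primary rate. This follows from the restriction in Measures of outcome together with the exclusion of mortality as an outcome.

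Its size is unknown. It is tempting to assume a share of infections present on admission and convert it into lost precision. The article supports no such share, and leaving those episodes out loses nothing from a hypothesis about hospital acquired infection. The conclusion assumes only that some bacteraemic admissions stay beyond 24 hours and are worked up on the unit, which the eligibility rule allows. It is a worthwhile, inexpensive improvement and does not undermine the primary analysis.

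**What to change.** 1. Keep hospital acquired, culture-positive episodes as the population for the nosocomial morbidity and cost hypothesis. State it in the same words in the Introduction, Objectives and hypotheses, and Measures of outcome, which now refer to septic shock, culture-proven bloodstream infection and hospital acquired episodes respectively.
2. Add a between-arm comparison of the same morbidity indicators, with mortality reported by arm, in all culture-proven bloodstream infections worked up in the trial, whatever their origin. Name it as the safety analysis for the discontinuation hypothesis, and assign arm by the plan's existing intention-to-treat rule. Count follow-up from the work-up, because a patient whose treatment was withheld has no start of antibiotics to count from.
3. Report this comparison as an estimate with a confidence interval. The number of episodes is unknown, and a non-significant difference would not by itself show safety.
4. State that the secondary-outcome criterion at the 12-month interim analysis still refers to the hospital acquired population, so that the addition does not alter the stopping rule.

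The cost is a more mixed population in the added analysis and a little more analysis work. The clinical data around cultures and the mortality data are already collected. Culture-negative infection and pneumonia would still lie outside this comparison, and the report should say so.

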**Methods:**

All patients admitted to the multidisciplinary neonatal and paediatric intensive care unit of a university children's hospital will be included. Patients will be allocated either to routine sepsis work up or to the intervention strategy with additional cytokine measurements. Physicians will be requested to estimate the pre-test probability of sepsis and pneumonia at initial suspicion. In the treatment arm, physicians will receive raw cytokine results, the likelihood ratio and the updated post-test probability. A high post-test probability will suggest that immediate initiation of antibiotic treatment is appropriate, whereas a low post-test probability will be supportive of watchful waiting or discontinuing prophylactic empirical therapy. Physicians may overrule the suggestions resulting from the post-test probability.

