### Data collection

Routine sepsis work up includes collection of blood cultures, other microbial specimens where appropriate, and measurements of white blood cell count, including differential and plasma levels of C-reactive protein. Routine surveillance for ventilator-associated pneumonia comprises microbiological examination of the tracheal aspirate, including cultures. As described above, physicians must provide two probability estimates, one for the presence of sepsis and one for pneumonia, whenever they order a sepsis or pneumonia work up. This ensures that clinicians state their estimate before knowledge of the test result. These estimates (pre-test probabilities) are integrated with cytokine concentrations derived from likelihood ratios for sepsis or pneumonia using Bayes' theorem. The algorithms for calculating post-test probabilities are presented in Table 1. A study nurse records clinical data for both groups on the day preceding collection of culture specimens and on the following 6 days (Fig. 3). We will collect data on mortality, but this will not be included as a study outcome because of low mortality rates and the intended study size. Further data are collected from the hospital's database. This database contains all physician's reports, patient baseline data, routine laboratory results, pharmacology data, costs per patient and day of specific medications (e.g. fresh frozen plasma), and staff allocation.

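### The secondary outcomes start their 7-day clock at antibiotic initiation, which the test result can move, and the safe-discontinuation hypothesis has no dedicated safety outcome

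*Protocol article*

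**What the plan says.** Measures of outcome (protocol article) defines the secondary outcomes "for all episodes of hospital acquired infection with positive blood cultures for the first 7 days following initiation of antibiotics", after adjustment for patient confounders. Two of them are counts of support-free days: "number of days free from mechanical ventilation (an indicator of respiratory failure); number of days free from inotropic support (an indicator of circulatory failure"). The other two are the cost of specific expensive medications and nurse allocation.

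The Methods paragraph of the Abstract describes how the result may act on treatment: "A high post-test probability will suggest that immediate initiation of antibiotic treatment is appropriate". For the opposite result, the same sentence says that "a low post-test probability will be supportive of watchful waiting or discontinuing prophylactic empirical therapy".

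Data collection uses a different anchor: "A study nurse records clinical data for both groups on the day preceding collection of culture specimens and on the following 6 days". It adds that further data come from the hospital database, and says of deaths: "We will collect data on mortality, but this will not be included as a study outcome", giving low mortality and the intended study size as the reason.

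Objectives and hypotheses sets two aims that depend on these outcomes. One is that surveillance "will allow safe discontinuation of antibiotic therapy within 24 hours" when the model indicates no infection. The other reads: "The second hypothesis we will test is whether early diagnosis reduces the morbidity and costs associated with hospital acquired infection". Under Stopping rules, the absence of a trend toward improved secondary outcomes at P < 0.1 is one of the two conditions for ending the trial at 12 months.

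**The concern.** A follow-up window should open at a moment the allocated strategy cannot influence. Here it opens at an event after allocation that the strategy is meant to bring forward in some episodes and to defer or avoid in others. If the arms differ in when antibiotics start, the same clinical course is viewed through different 7-day windows. A culture-positive episode that is never treated has no window at all.

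At stake are the test of the second hypothesis and one of the two conditions in the 12-month discontinuation rule. An artefactual trend could keep the trial running. A masked trend could contribute to ending it, if antibiotic use also showed no trend.

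The second issue is the word safe in the first hypothesis. The patients to whom it applies are those whose antibiotics are withheld or stopped, and no outcome is designated to show whether they came to harm.

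**Working it through.** The plan gives no figure for the secondary outcomes, so there is none to reproduce. Its 2300 days per arm concern the primary outcome and are not used here.

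**Step 1: the two anchors side by side.**
- Outcome window: 7 days from antibiotic initiation (Measures of outcome).
- Nurse recording: from the day before culture (Data collection). The wording can be read as the preceding day plus six, ending on day +5, or as six days after the culture day, ending on day +6.
- The anchors coincide only when antibiotics start on the culture day.

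**Step 2: can allocation affect the anchor?** Culture sampling: not at the index work-up. Under Randomization, physicians learn the day's status 30 minutes after the 10 a.m. sample deadline. Antibiotic initiation: yes, on the Abstract's description, because it can follow the result.

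**Step 3: do the planned safeguards repair this?** Confounder adjustment deals with differences between patients, not with misaligned windows. The intention-to-treat rule in the sample size section decides which arm a treatment course belongs to, not when its clock starts.

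**Step 4: effect of moving the anchor, by hand.** Let support run from time *a* to *b* after first suspicion and the window from *t* to *t* + 7.

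Free days = 7 − [min(*b*, *t* + 7) − max(*a*, *t*)], with the bracket set to zero if negative.

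Assume 4 days of support, the same course in both arms, control antibiotics at day 2 and intervention antibiotics at day 0.
- Support from day 0 to 4. Control: 7 − (4 − 2) = 5. Intervention: 7 − (4 − 0) = 3. Difference −2.
- Support from day 5 to 9. Control: 7 − (9 − 5) = 3. Intervention: 7 − (7 − 5) = 5. Difference +2.

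The courses are identical, yet the artefact has opposite signs.

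**Step 5: the same, averaged.** This is a simulation of 400,000 episodes with support duration gamma distributed (shape 2, scale 2, mean 4 days), control antibiotics at day 2 and no treatment effect. Entries are intervention minus control mean free days out of 7.

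| Antibiotics earlier by (days) | Support begins 0–2 days after suspicion | Support begins 2–5 days after suspicion |
|---|---|---|
| 0 | 0.00 | 0.00 |
| 0.5 | 3.82 − 4.17 = −0.35 | +0.14 |
| 1 | 3.59 − 4.17 = −0.58 | +0.30 |
| 2 | 3.51 − 4.17 = −0.66 | +0.72 |

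With the window anchored at the work-up, both arms have the same mean (3.51 in the first scenario), so the difference is zero by construction. The support times and delays are assumptions; the article gives none.

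**Step 6: the safety hypothesis.** Every secondary outcome is limited to hospital-acquired, blood-culture-positive episodes. The Introduction names ventilator-associated pneumonia as the unit's most frequent reason for antibiotics; without a positive blood culture it lies outside that set. Mortality is recorded but is not an outcome. No outcome is therefore designated for harm among patients in whom stopping or withholding is suggested.

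**The case against.** The strongest reply is that the gap between culture and antibiotics may often be close to nil. The Introduction describes a low threshold for empirical therapy, the Design section ties the work-up to any antibiotic prescription, and the Intervention strategy section speaks only of stopping or continuing. This stands as a limit on size: where antibiotics start at culture, the anchor hardly moves. It does not remove the problem, because the Abstract includes initiation and watchful waiting, and the second hypothesis works through earlier diagnosis.

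A reader might infer more than the documents support:

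- *That the outcomes are biased in a known direction, or that the benefit is removed.* Support days after a late start still count, and the artefact can take either sign.
- *That part of the window is lost, and more so in one arm.* The hospital database holds physicians' reports, pharmacology data, daily costs of specific medications and staff allocation. Costs and nurse allocation are therefore not confined to the nurse's days, and inotropes could plausibly be recovered. Ventilation is not listed by name. No delay by arm is given, and watchful waiting could make either arm the later one.
- *That deaths inflate free days.* The article states no scoring rule, and an analysis plan not shown may contain one.
- *That restriction to positive cultures selects by arm.* It does not at the index work-up, since samples are due before the arm is disclosed.
- *That culture-negative episodes have no outcome.* The primary outcome and the antibiotic-free-day analyses after any work-up or any initiation include them, and a re-start would reduce those free days. A wrongly stopped patient with a hospital-acquired positive blood culture can also enter the secondary set. What is missing is narrower: a dedicated safety outcome.

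**Conclusion.** The point holds in two parts. First, the time origin of all four secondary outcomes is an event after allocation that the intervention can move, and it differs from the anchor of the nurse-recorded data. The comparison can be distorted in either direction by an amount the documents do not determine. The averaged illustration (−0.66 to +0.72 days out of 7) rests wholly on assumed support times and on antibiotics starting 0.5 to 2 days earlier in one arm; it shows that the artefact exists and is not an estimate for this trial. Second, safe discontinuation is stated as a hypothesis without a dedicated safety outcome in the patients concerned. Low mortality is a fair reason not to power the trial for death, but not for leaving that hypothesis without a safety outcome.

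The primary outcome is unaffected. The change should be made because these outcomes carry the second hypothesis and feed the discontinuation rule.

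**What to change.** In Measures of outcome, start the window on the day of culture sampling for every hospital-acquired, culture-positive episode. Attribute the episode to that day's allocation, regardless of whether or when antibiotics start. State the last recorded day explicitly (day +5 or day +6), and either set the window to that length or complete the remaining day from the hospital database.

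Add descriptive safety outcomes for all work-up episodes, by arm and with confidence intervals: the deaths already collected, antibiotic re-starts and new positive blood cultures.

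The cost is small: revised wording, a few extra tables and possibly a database look-up for the last day. Antibiotic management does not change, and the nurse's recording is already anchored on culture.

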## Abstract

**Introduction:**

Bacterial infection represents a serious risk in neonates and critically ill paediatric patients. Current clinical practice is characterized by frequent antibiotic treatment despite low incidence of true infection. However, some patients escape early diagnosis and progress to septic shock. Many new markers, including cytokines, have been suggested to improve decision making, but the clinical efficacy of these techniques remains uncertain. Therefore, we will test the clinical efficacy of a previously validated diagnostic strategy to reduce antibiotic usage and nosocomial infection related morbidity.

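### No outcome counts bloodstream infection that arises after antibiotics are withheld or stopped, although the first hypothesis includes safe stopping within 24 hours

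*Protocol article*

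**What the plan says.** Only the protocol article is at hand.

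- **Measures of outcome.** The primary outcome is the rate of systemic antibiotic use per 1000 hospitalization days. The four secondary outcomes are ventilation-free days, inotrope-free days, costs of certain expensive drugs, and nurse allocation. All four are taken "for all episodes of hospital acquired infection with positive blood cultures for the first 7 days following initiation of antibiotics", after adjustment for patient confounders. Neither the number nor the rate of such episodes is listed.
- **Data collection.** Mortality is recorded but is not an outcome. A study nurse records clinical data from the day before cultures are taken through the 6 days after.
- **Objectives and hypotheses.** The first hypothesis is that antibiotics can safely be discontinued within 24 hours if the prediction model indicates no infection. The second asks "whether early diagnosis reduces the morbidity and costs associated with hospital acquired infection", and the section adds: "Ascertaining relevant indicators of morbidity and costs in all patients with culture proven bloodstream infection will operationalize this".
- **Randomization.** The unit is the calendar day. Physicians learn the day's status 30 minutes after the 10 a.m. sample deadline.
- **Sample size calculation and statistical considerations.** Each antibiotic course is allocated to the status of the day on which the decision to withhold or continue had to be made.
- **Stopping rules.** At 12 months the trial is discontinued if there is no trend in antibiotic treatment and no trend at P < 0.1 toward better secondary outcomes.

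**The concern.** A shorter course on intervention days is the effect the trial hopes to show. The way it could do harm is that a patient whose antibiotics were withheld or stopped later develops a culture-proven infection. The primary outcome measures antibiotic use only. The secondary outcomes describe how severe a bloodstream infection is once it exists, and none records whether one followed the decision.

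Allocation by day adds a second difficulty. The later infection has its own work-up, on a day with its own status. It therefore joins the secondary outcomes under that day's arm, and nothing ties it back to the decision that may have led to it.

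At stake is the safety half of the first hypothesis. The trial could report fewer antibiotic days and unchanged, or even better, secondary outcomes while early stopping was causing infections.

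**Working it through.** **1. The plan's own figure.** The article gives one base sample size, 2300 days per arm for the primary outcome (40% antibiotic use, 10% relative reduction to 36%, 5% error, 80% power). With p̄ = 0.38:

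n = [1.96·√(2·0.38·0.62) + 0.8416·√(0.40·0.60 + 0.36·0.64)]² / 0.04² = (1.345 + 0.577)² / 0.0016 ≈ 2311 (two-sided).

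The figure reproduces within 3%. The present point does not depend on it. The article gives no event count or power for the secondary outcomes, so every count below is an assumption.

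**2. Follow one infection through the rules.**

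- Day D is an intervention day. Cultures are taken by 10 a.m., the status is disclosed 30 minutes later, results return before 1 p.m., and antibiotics are stopped.
- Some days later the patient deteriorates. New cultures are taken and are positive, and a new course starts.
- That course has its own decision day. The allocation rule gives it to that day's status, whatever the status of day D.
- Day D's arm shows no infection in any listed outcome. At most it shows antibiotic days.

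**3. Size under own-day counting.** Assume 30 episodes per arm, 4 ventilator-free days (so 7 − 4 = 3 ventilated days) per episode, and 15 extra episodes caused by stopping on intervention days. The plan has equal arms of 3000 days. If the status of the later day is unrelated to that of day D, half of the 15 are expected in each arm.

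| Counting rule | Intervention | Control | Difference |
|---|---|---|---|
| Own work-up day | 30 + 7.5 = 37.5 | 30 + 7.5 = 37.5 | 0 |
| Extra episodes by decision day | 15 | 0 | 15 |

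The per-episode means also move together. If the extra episodes are mild (6 free days), each arm's mean is (30·4 + 7.5·6)/37.5 = 4.40, and the difference is 0.

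**4. Size if the extra episodes fall unevenly.** The extreme case puts all 15 on intervention days.

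- *Equal severity.* The mean stays at 4.0 in both arms. Ventilated days per 1000 are 45·3/3 = 45 against 30·3/3 = 30.
- *Milder (6 free days).* The intervention mean is (30·4 + 15·6)/45 = 4.67 against 4.0. Ventilated days per 1000 are (30·3 + 15·1)/3 = 35 against 30. The outcome improves while the burden rises.

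The second case is the bound, not the expectation. Uneven splits between steps 3 and 4 give intermediate results.

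**5. Precision to expect.** For k events in each arm, the 95% interval for a rate ratio spans a factor of exp(1.96·√(2/k)): 1.66 for k = 30 and 1.32 for k = 100. Power to detect a ratio of 1.5 is Φ(ln 1.5/√(1/e + 1/(1.5e)) − 1.96), with e the number of control events: about 23%, 41% and 68% for e = 15, 30 and 60. Infections following an index decision are a subset of all episodes, so the lower figures are the more relevant ones.

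**The case against.** **The restriction is declared and suits the second hypothesis.** This stands. The article ties that hypothesis to earlier diagnosis, which acts on severity once a patient is infected, and it names culture-proven patients as the set.

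**A reader might infer more.** The arm-level wording in the Introduction, "the arms will not differ with respect to costs associated with hospital acquired septic shock", and the Abstract's aim "to reduce antibiotic usage and nosocomial infection related morbidity" could suggest that the second hypothesis concerns the whole burden of infection, so that episodes must be counted and the hypothesis decided from arm totals. The documents do not support that. They nowhere speak of overall burden, and they do not say whether costs and nurse allocation are averaged per episode or summed. A sum would show a change in number. (Summed free days would mislead: 45 episodes against 30 at 4 days each give 180 against 120, so more infections would look better.)

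**Culture positivity is mostly fixed before the arm can act.** This stands for the index culture, which is taken before the status is disclosed. Restricting to positive index cultures is therefore close to a baseline subgroup, and a count of episodes by the day they open would mostly add chance variation. It does not hold for infections that arise after the decision, and those are the gap.

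**Antibiotic-free days already register a relapse.** The planned analyses over the 4 days after a work-up and the week after starting antibiotics would lose days when treatment is restarted. But those days are netted against the days saved by stopping early, and a restart is not a culture-proven infection. The safety signal is not visible separately.

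**Power would be low.** True, as step 5 shows. That is a reason to report an interval and conclude cautiously, not to leave the outcome out.

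**Conclusion.** The point holds in this form: no listed outcome captures culture-proven infection after antibiotics were withheld or stopped, while safe discontinuation within 24 hours is a stated hypothesis. Under own-day counting, the expected difference from such infections is zero whatever their number, provided the status of the later day is unrelated to that of the decision day. If they fall unevenly, per-episode means can stay flat or improve (4.0 to 4.67 in the assumed example), and an improvement reaching P < 0.1 would by itself prevent discontinuation at the interim analysis.

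Two stronger readings go too far. The documents do not support saying that the second hypothesis cannot be answered, because its restriction to culture-proven patients is stated openly. Nor does a change in the number of infections always show as no difference; that requires an unchanged severity mix or an even split between arms.

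The sizes rest on assumed counts and severities. The mechanism rests only on the outcome list, the unit of randomization and the allocation rule. The addition is worthwhile and cheap; the primary comparison is unaffected.

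**What to change.** In Measures of outcome, add one secondary (safety) outcome: the proportion of work-ups (or of antibiotic courses; choose one) followed by a new blood-culture-positive episode within a fixed window. The 6 days after culture collection already recorded under Data collection would serve. Define new as a positive culture taken after the decision day.

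Allocate each work-up by the rule already in the statistical section, to the status of the day on which the decision to withhold or continue was made. State how an infection preceded by more than one decision day is handled, for example by linking it to the last one. Report the difference between arms with its confidence interval beside the per-episode outcomes, and do not read a non-significant result as proof of safety. The second hypothesis and its four outcomes can stay as they are.

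The cost is a few sentences, a linkage rule and one table; culture results and the days after each work-up are already collected. The downsides are few events and hence a wide interval, and some dilution when a later day in the other arm changes management before the infection appears.
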